## Scientific justification of the research

Literature has focused extensively on the psychiatric and psychological dimensions of Multiple Sclerosis (MS) (Gay et al., 2017). People with MS have a higher prevalence of anxiety and depression than the general population (Marie et al., 2017). Developing a sense of coherence and control over their illness has been positively associated with people with MS' emotional, psychological and social wellbeing (Bassi et al., 2016; Calandri et al., 2018). The role of psychological interventions in these processes has been explored in previous research and the results indicate how interventions such as Cognitive Behavioural Therapy, Mindfulness and Acceptance and Commitment Therapy have moderate effects on fatigue, pain, resilience, positive affect, anxiety, depression and stress management (Alscher et al., 2020; Moss – Morris et al., 2021; Pakenham et al., 2018; Taylor et al., 2020).

Previous research is mainly based on quantitative outcome measures to capture change processes as a result of the interventions. The findings present the effects of these generic models on psychological and physical facets of MS. However, little is known about the experience of people with MS that take part in these interventions and especially about their needs and preferences with regards to psychological programmes involved in their care. The current study follows from a mixed method longitudinal exploratory study on the experience of psychosocial interventions for 20 people with MS ([name] et al., 2022). The findings of the study revealed the trajectories of people with MS from diagnosis through their engagement into individual and group psychological interventions of their choice in the community. Forgiveness, empowerment and familiarisation with the new body contributed to feelings of relief with a significant impact on improvement of physical functioning, perception of general health and reduction of anxiety ([name] et al., 2022).

The novel intervention MyMS-Ally developed for the current project adopted a process – based approach (Hofmann & Hayes, 2019). Intervention techniques and processes were informed by aspects of established therapeutic approaches as they have been found effective for people with MS based on previous research conclusions. In addition to this, the goal of the current research project is to move away from theory – based interventions and towards a patient – led perspective of intervention development and implementation. We followed the trend in recent literature on clinical therapy processes to move from nomothetic to idiographic approaches of research and intervention (Hofmann & Hayes, 2019). As we have been developing MyMS-Ally group psychological intervention, our aspiration has been to establish processes that correspond to procedures, needs and characteristics of people with MS (Hofmann & Hayes, 2019). Thus, the structure of this intervention has also been based on what people with MS have found significant, helpful and beneficial in their accounts of their experience of psychological interventions they have engaged into ([name] et al., 2022). The themes represented the change processes from the people with MS’ perspective as they related them to intervention processes. These themes guided the development of the novel psychological group intervention MyMS-Ally.

Following the systematic development of the intervention, it needs to be tested carefully through pilot feasibility and acceptability studies in order to address uncertainties and make appropriate modifications before further evaluation of the intervention (Medical Research Council Guidance). The current study will provide valuable information on how the intervention will be appraised by participants that take part, on helpful and unhelpful aspects of the intervention based on the participants’ experiences and accounts as well as the feasibility of implementation of the intervention in the context of the service. Moreover, adherence to outcome measures and study processes will also be assessed which will give valuable information for the design of the consequent evaluation study (Craig et al., 2008).

## **Research design and methodology**

This is a mixed – method pilot design with the aim to explore feasibility and acceptability of the novel group psychological intervention MyMS-Ally. Quantitative and qualitative data will be collected in order to facilitate analysis of people with MS’ experience of the intervention as well as analysis of outcomes on quality of life, anxiety, depression and emotion regulation. The mixed-method design offers the framework for statistically significant conclusions to be made but also incorporate participants’ meaning – making accounts with an in-depth description of their experience of the intervention. The study adheres to an idiographic paradigm of exploring the impact of the intervention (Haynes et al., 2009; Molenaar, 2004) where each participant’s variations and changes over time are investigated through multiple points of collecting data. Following the patient – centred regime of the development of the intervention and the evaluation processes, the aim of the researchers is to identify tailored assessment processes that will eventually shed light on changes over time within each participant. Quantitative and qualitative methods are “compatible partners” in this research context (Onghema et al., 2019, p. 463) following a pragmatism epistemology combining action and reflection (Biesta 2010).

## **Participants**

Recruitment and implementation of the intervention will take place in the Bristol and Avon Multiple Sclerosis Centre in Southmead Hospital, Bristol. A group of 5 - 6 participants will be recruited to take part in the MyMS-Ally group intervention. The group size reflects the minimum number of members of a group psychological intervention for meaningful interactions to be unfolded and the maximum number which allows enough time and space for each member to use the group effectively (Saracutu et al., 2018). The size of the sample also reflect the recommendations made in the PPI involvement focus group. Should more people with MS express interest in taking part, more than one groups will be offered. Eligible participants will be aged 18 years or above, diagnosed with multiple sclerosis more than two years ago, able to read, write and speak English and able to engage into eight weekly group psychological intervention sessions (2 months). The group intervention as well as data collection processes will take place online therefore access to the internet and to a device where they can use Microsoft Teams software on are required. People with MS with suspected and/or diagnosed comorbidity with Depression, Bipolar Disorder or Psychotic Disorders will not be able to participate in the study.

Recruitment will be carried out in collaboration with the team of professionals of the Bristol and Avon Multiple Sclerosis (BAMS) Centre in Southmead Hospital, Bristol. The study as well as the inclusion and exclusion criteria of the sampling will be presented to the team in a meeting. An information package will also be given to the team of professionals with relevant information on the intervention, study processes and participant eligibility. The professionals will identify patients that meet the eligibility criteria and inform them of the study. The potential participants will be given the Participant Information Sheet and the Consent Form at that point as they reflect on whether or not they are interested in taking part. People with MS who are interested in participating will contact the chief investigator (CI) who will arrange individual meetings with them to discuss the study procedures and the intervention process, the eligibility criteria as well as answer any questions they might have. The people with MS who will agree to participate will have to return the signed consent form to the CI before the commencement of collection of data and intervention.

### ***MyMS-Ally group intervention***

The intervention has been developed based on previous research conclusions, systematic reviews and meta – analyses about what is helpful for people with MS in the field of psychological intervention programmes. Moreover, following the patient – centred paradigm, the intervention is based on people with MS' accounts on change processes in their experience and management of MS in relation to intervention processes. MyMS-Ally group intervention will last for two months and participants will be asked to attend weekly sessions

that will last 1 ½ hours each (8 sessions). The details of the intervention are outlined in the attached document in this IRAS application. The intervention will take place online following the PPI involvement group recommendation. Following the PPI involvement focus group discussion, it will be ensured that the pace and the needs of the participants will be taken under account during the implementation of the intervention. For example, the facilitator will establish breaks during the sessions for the participants to take time and move away from their monitors as well as incorporate overviews and summaries of previous sessions in the discussions in the group.

### ***Data collection***

Feasibility and acceptability of the processes of the novel group intervention MyMS-Ally will be explored mainly through the qualitative interviews. The participants will attend three qualitative semi-structured interviews:

1. At baseline, before commencement of the intervention: This interview will focus on the experience of their Multiple Sclerosis and the expectations they have from MyMS-Ally group intervention (prospective acceptability, Sekhon et al., 2017).
2. At the end of the intervention (at the end of the 8 sessions): This interview will focus on satisfaction, on helpful and unhelpful aspects of the intervention as they experienced them, what facilitated them to complete the programme and any impact they perceived the intervention had on their experience and management of their Multiple Sclerosis (Sekhon et al., 2017).
3. At three months follow – up: This interview will focus on their experience of MyMS-Ally intervention and the impact it might have on their experience and management of their Multiple Sclerosis.

Interviews are expected to last approximately one hour and they will take place online on a platform with encryption where recordings are possible (Microsoft Teams) and stored on the CI's university (UWE) onedrive in a password protected folder.

Additional indicators will be recorded in order to explore further the feasibility and acceptability of MyMS-Ally intervention (Saracutu et al., 2018):

- Number of people with MS referred by the health and mental health professionals of the service.
- Number of people with MS attending the screening meetings with the Chief Investigator.
- Time taken to complete the questionnaires and missing data.
- Follow up responses (1 month and 3 months follow up).
- Number of sessions attended by the participants.
- Feedback from MyMS-Ally group intervention facilitator.

Participants will be asked to complete three questionnaires for the collection of quantitative data and to address the secondary objectives of the study. The aim is to collect preliminary data on outcomes and impact of the intervention on quality of life, anxiety, depression and emotion regulation. Quality of life, anxiety and depression have been extensively used as indicators for change in the literature of evaluating psychological interventions for people with MS. Emotion regulation is a factor that needs to be explored further as it has been associated with the wellbeing of people with autoimmune diseases (Karademas et al., 2020). The questionnaires participants will be asked to complete are:

- **Satisfaction with Life Scale (SWLS):** The satisfaction with life scale was developed to assess the participants' satisfaction with life as a whole (Diener et al., 1985). It comprises of five items. It has shown sufficient sensitivity to detect change in life satisfaction during the course of a clinical intervention (Pavot & Diener, 1993) and in the field of health psychology it has been used to evaluate subjective quality of life (Pavot & Diener, 2008). The items are global rather than specific in nature. Statements are rated on a 7-point Likert scale (1 strongly disagree, 7 strongly agree).
- **Hospital Anxiety and Depression Scale (HADS):** The HADS is a self – report scale assessing the states of depression and anxiety. Participants are asked to reflect on how they have been feeling during the past week. The scale comprises of 14 items, seven for anxiety and seven for depression. The scale has demonstrated good factor structure and internal consistency (Mykletun et al., 2013). The scale has also been used in research with people with MS (Nazari et al., 2020).
- **Emotion Regulation Questionnaire (ERQ):** A 10-item scale designed to measure respondents' tendency to regulate their emotions in two ways: (1) Cognitive Reappraisal and (2) Expressive Suppression. Respondents answer each item on a 7-point Likert-type scale ranging from 1 (strongly disagree) to 7 (strongly agree). Higher scores in the reappraisal scale indicate better ability to monitor, evaluate, and reduce distress. In contrast, higher scores in the suppression scale indicate poorer ability to repair mood and to manage stressful situations. Overall, the ERQ has very good psychometric properties with a definite two-factor structure, good internal consistency (0.83 and 0.79 for reappraisal and suppression, respectively), and satisfactory test–retest reliability (Gross & John, 2003). Cognitive reappraisal has been associated with wellbeing for people with Multiple Sclerosis (Karademas et al., 2018) and has been used to assess psychological states and quality of life for people with MS (Phillips et al., 2009; Sadeghi et al., 2021).

A significant advantage of the questionnaires chosen is that they are brief (it takes about 10 – 15 minutes to complete). Participants will be asked to complete the questionnaires four times during the course of the study:

1. At baseline, before commencement of the intervention
2. At the end of the intervention
3. At one month follow up after the end of the intervention
4. At three months follow up after the end of the intervention

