### ***Risks, burdens and benefits***

No serious adverse events are expected as a result of the study design and procedures. However, incidents might take place during the course of the study and the implementation of the psychological intervention:

- Participants might find the participation in a group intervention distressing and tiring.
- Participants might find the quantitative data collection process burdensome.
- Participants might not be able to attend the individual qualitative interviews.
- The group facilitator and the supervisor might make the decision that one or more participants cannot engage into the group intervention with the rest of the members.

The intervention and the study processes have been designed in a way that they respect the participants' needs and characteristics. The research team will follow the participants' pace and will take under consideration factors such as cognitive and physical fatigue in the intervention implementation and data collection processes. Following the PPI involvement input, the intervention and data collection processes will take place online and will be implemented in a flexible way to accommodate participants' needs. Therefore, should any participant miss a session during the intervention implementation because of health issues they will still have the opportunity to continue taking part in the intervention and the study.

Should any of the above adverse events occur, the participants have the right to withdraw from the study without having to justify their decision. If a participant withdraws, the CI will arrange for a check – in meeting with them if they accept the invitation and support resources will be provided to all participants in the Participant Information Sheet. Moreover, all data from participants that withdraw from the study will not be used in the analysis and will be destroyed along with any personal details.

The benefits for participants entail:

- It is aspired that participants will experience the benefits of the intervention in their experience and management of MS, their quality of life and emotion regulation.
- Taking part in a novel group psychological intervention which has been developed by people with MS' accounts of needs and preferences, psychotherapy theory and consultation with practitioners.
- Contributing to ameliorating and finalising the intervention protocol which will be disseminated to patients and practitioners involved in the care of people with MS.

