### ***Conflict of interest***

The roles of each member of the research team are clearly defined. The CI is the lead researcher of the study and is not involved in the implementation of the group psychological intervention MyMS-Ally or the collection of the qualitative data. The group facilitator will be a trained practitioner who will be supervised by a senior practitioner and they will comprise the clinical team of the study who will not be involved in the collection and analysis of the data. The qualitative interviews will be conducted by an experienced independent researcher. Therefore, research and clinical processes are clearly separated in the course of the study. The CI's identity as a Chartered Counselling Psychologist and her clinical skills will be implemented in order to create safe and respectful environments for participants in the processes of intervention implementation and collection of data.

At the end of the study participants will have the opportunity to meet with the CI for check – in meetings should they accept the invitation. The final results of the study will also be fed back to the participants should they accept the report. Data will be stored in the University of the West of England Research Repository and will be reserved there as restricted data accessed by third parties for purposes of review. The participants' personal details will be destroyed according to guidelines.

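### Distress, tiredness and removal from the group are called adverse events, yet no listed indicator counts them, and data from participants who withdraw are destroyed

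*Protocol*

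**What the plan says.** Both risk sections (in the Summary of Main Issues and again after Methods of Analysis) list four possible incidents. Two concern the intervention: "Participants might find the participation in a group intervention distressing and tiring", and "The group facilitator and the supervisor might make the decision that one or more participants cannot engage into the group intervention". The other two concern data collection: questionnaire burden and inability to attend interviews. The sections then label all four and state the response: "Should any of the above adverse events occur, the participants have the right to withdraw from the study". If a participant does withdraw, all their data are left out of the analysis and destroyed.

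Data collection makes the interviews the main source on feasibility and acceptability, and adds: "Additional indicators will be recorded in order to explore further the feasibility and acceptability of MyMS-Ally intervention". The six indicators are referrals, screening attendance, questionnaire completion time with missing data, follow-up responses, sessions attended, and "Feedback from MyMS-Ally group intervention facilitator". The end-of-intervention interview covers satisfaction, helpful and unhelpful aspects, perceived impact and "what facilitated them to complete the programme".

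Conflict of interest describes the facilitator and supervisor as a clinical team "who will not be involved in the collection and analysis of the data". The planned size is given under Participants: "A group of 5 - 6 participants will be recruited to take part in the MyMS-Ally group intervention", with further groups only if interest allows.

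**The concern.** Acceptability is half of the primary objective, and the Principal question section ties it to emotional and cognitive responses and to the appropriateness of the intervention. Distress, exhaustion and removal from the group bear directly on that, and the protocol itself foresees them. Yet the plan does not say that they will be recorded, counted or reported. The people best placed to see them during sessions are the facilitator and supervisor, whose part in the data is described inconsistently. The people most likely to have been affected are those who withdraw, and their data are destroyed.

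The results are meant to guide changes to the intervention before further evaluation. A report that mentions no adverse events could mean that none happened, that none were written down, or that the records were erased. No later analysis plan could tell these apart, because what is not collected, or is destroyed, cannot be recovered.

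**Working it through.** The protocol states no harm rate or calculated sample size, so there is no figure to reproduce. The main check sets the sections side by side.

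**Step 1: named risks against the indicators.**
- Questionnaire burden: tracked by completion time and missing data.
- Missed interviews: partly tracked by follow-up responses.
- Distress or tiredness from the group: no count. Sessions attended may reflect it indirectly, but no reason for absence is recorded, so absence through distress looks the same as absence through an unrelated health problem.
- Removal from the group: no count.

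**Step 2: other routes by which the two intervention risks could surface.**
- *Facilitator feedback* is listed with no content or timing, and the Conflict of interest section appears to contradict it.
- *HADS* is given at baseline, end of intervention, one month and three months, and asks about the past week. None of these falls during the course of sessions. The Quantitative Data section plans means, standard deviations and within-subject effects, not individual events.
- *End interview* asks about unhelpful aspects, but retrospectively. Eight weekly sessions span seven intervals, so session 1 lies at least 7 weeks back. One topic is what helped people complete; none is described for those who stopped.
- *Risk assessment* by the chief investigator, independent researcher and facilitator is stated in the later risk section. High risk leads to notifying the referring professional, but no study record or report of this is described.

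**Step 3: size.** Inputs: n = 5 or 6 (Participants), 8 sessions (MyMS-Ally group intervention).
- Person-sessions: 5 × 8 = 40; 6 × 8 = 48.
- One affected participant: 1/6 = 17%; 1/5 = 20%.
- One distressed participant withdraws from a group of six and the data are destroyed: the true 1/6 (17%) becomes 0/(6 − 1) = 0/5.

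**Step 4: what a count could show.** With zero events, the one-sided 95% upper limit p solves (1 − p)^n = 0.05, so p = 1 − 0.05^(1/n).
- n = 5: 1 − 0.05^(1/5) = 45.1%.
- n = 6: 1 − 0.05^(1/6) = 39.3%.

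The chance of at least one affected participant is 1 − (1 − p)^n. The rates below are assumptions, since the protocol gives none.

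| Assumed rate | n = 5 | n = 6 |
|---|---|---|
| 10% | 41.0% | 46.9% |
| 20% | 67.2% | 73.8% |
| 30% | 83.2% | 88.2% |

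A count at this size cannot exclude a substantial rate, but a common problem would probably appear in it.

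**The case against.** The best defence is that this is a small, mainly qualitative study. Each participant is interviewed three times, the analysis is case by case, and whether the intervention was felt to be helpful or unhelpful is an explicit focus. With five or six people, that is a legitimate way to learn about negative experience, and a count adds little precision. The interview schedule and intervention details are not in the document, so they may prompt for or log more than is visible. This stands in part: it limits the point to counting and retention, and does not show that negative experience is ignored.

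A reader might go further in several directions that the document does not support:
- *That nothing collected touches distress.* HADS measures anxiety and depression, and facilitator feedback and the interviews could carry such events in unstructured form.
- *That none of the named risks is tracked.* The two data-collection risks are, at least partly.
- *That the facilitator is simply barred from contributing.* One section excludes the clinical team from data collection and another lists their feedback. A facilitator may be read as an informant rather than a data collector, so this is a conflict to reconcile.
- *That recall is much longer than 7 weeks.* The timetable gives only months, so no longer interval can be fixed from it.
- *That a fatigue questionnaire is needed.* Brevity was a deliberate choice to limit burden, and a session record would suffice.

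It can also be objected that entries in a log would be destroyed when a participant withdraws. That is correct, and any remedy has to deal with the destruction rule as well.

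**Conclusion.** The point holds in a limited form. The protocol names two intervention risks as adverse events but provides no count of either, records attendance without reasons, contradicts itself on the facilitator's contribution, and destroys the data of those who take the exit it offers. Acceptability could then be judged on those who stay, with one event among six (17%) reported as none among five.

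That example assumes a single group of six and that the affected person withdraws from the study rather than only missing sessions. The document does not say whether someone removed from the group counts as withdrawn. The change should be made because it is cheap and the information cannot be recovered later. It would not make the study able to estimate a harm rate.

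**What to change.** 1. **Data collection:** add a brief session log kept by the facilitator, with one line per participant: attended, left early, missed (with the reason if volunteered), distress or fatigue that interrupted participation, removal decision, risk notification made. Report it descriptively beside acceptability, as counts of participants and of person-sessions, and note that zero events among 5 or 6 people is compatible with rates up to about 45% or 39%.
2. **Conflict of interest and Data collection:** reconcile the two, so that the clinical team supplies the log and the listed feedback but does not interview, administer questionnaires or analyse.
3. **Both risk sections and the consent information:** state that a de-identified count of withdrawals and removals, with reasons if volunteered, is kept and reported even when other data are destroyed.
4. **End interview:** word it to cover unwanted or distressing effects and, for non-completers willing to talk, why they stopped.

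These changes concern recording and reporting only; they set no rule for managing participants. The cost is a one-page log, a few minutes of facilitator time per session, small wording changes, and a slight loosening of the separation between research and clinical roles.
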